##### Well-being

Well-being will be assessed by the 5-item WHO-5 Well-Being Index (WHO-5) (48) answered on a 6-point Likert Scale with scores ranging from 0 to 30 (α = 0.82) (49).

##### Quality of life

To measure quality of life, we will use the Assessment of Quality of Life Instrument (AQoL-8D) (50, 51), which consists of 35 items with eight dimensions: independent living (α = 0.9, ICC = 0.86), pain (α = 0.85, ICC = 0.86), senses (α = 0.69, ICC = 0.51), mental health (α = 0.84, ICC = 0.89), happiness (α = 0.85, ICC = 0.90), coping (α = 0.80, ICC = 0.79), relationships (α = 0.73, ICC = 0.88), self-worth (α = 0.85, ICC = 0.81) (51). Psychometrics properties have been shown to be acceptable.

##### Work limitations

To measure the on-the-job impact of chronic health problems and/or treatment with a focus on assessing limitations while performing specific job demands, the Work Limitations Questionnaire (WLQ) (52) is applied. It consists of 25 items on a 5-point Likert Scale, assessing four dimensions of work limitation. Walker et al. (53) report a Cronbach's alpha range of 0.83–0.88 (53).

##### Costs associated with psychiatric illness

Other measures related to the intervention include the Trimbos Questionnaire for costs associated with psychiatric illness (TiC-P) (54), including healthcare utilizations and productivity losses, adapted to the German health care system. It consists of 14 yes/no questions to assess contacts with healthcare providers of any kind and five items covering reduced efficiency and/or absence from work due to a psychiatric condition. The TiC-P has been proven to be a feasible and reliable instrument for measuring healthcare utilization and productivity loss (55). The German adaption has been utilized in a substantial number of randomized controlled trials as a basis for health economic outcome evaluations (56–67).

##### Training and acceptability

User satisfaction will be assessed by a questionnaire based on the Client Satisfaction Questionnaire (CSQ-8) (68), adapted to assess user satisfaction in online interventions (69). Global client satisfaction with the internet- and mobile-based intervention is measured by eight items. Previous research indicated good psychometric properties (α = 0.84–0.97) (70).

#### Other Assessments

Other assessments include demographics (e.g., age, gender, occupation, level of education) and current and previous experience with psychotherapy, self-esteem via Rosenberg Self-Esteem Scale (RSES) (71) and social phobia via Mini Social Phobia Inventory (Mini-SPIN) (72). For an overview of all outcome measures, see Table 3.

**Table 3 T3:** Overview study self-report assessments.

**Construct**	**Questionnaire**	**T1**	**T2**	**T3**	**T4**
Demographics	Socio-Demographic Data	✓	–	–	–
Internet addiction	Internet Addiction Test (IAT)	✓	✓	✓	✓
	Compulsive Internet Use Scale (CIUS)	✓	✓	✓	✓
Depression	Patient Health Questionnaire (PHQ-9)	✓	✓	✓	✓
Anxiety	General Anxiety Disorder Measurement (GAD-7)	✓	✓	✓	✓
Alcohol abuse	The Alcohol Use Disorders Identification Test (AUDIT-C)	✓	✓	✓	✓
Sleep	Insomnia Severity Index (ISI)	✓	✓	✓	✓
Worries	Penn State Worry Questionnaire – Ultra Brief Version (PSWQ-3)	✓	✓	✓	✓
Self-esteem	Rosenberg Self Esteem Scale (RSES)	✓	–	–	–
Social phobia	Social Phobia Inventory (Mini-SPIN)	✓	–	–	–
Procrastination	General Procrastination Scale—Short Version (GPS-K)	✓	✓	✓	✓
Gambling	Kurzfragebogen zum Glücksspielverhalten (KFG)	✓	✓	✓	✓
Wellbeing	WHO-5 Wellbeing Index (WHO-5)	✓	✓	✓	✓
Quality of life	Assessment Quality of Life (AQoL-8D)	✓	✓	✓	✓
Work limitations	Work Limitations Questionnaire (WLQ)	✓	✓	✓	✓
Health economic evaluation	Trimbos Questionnaire for Costs Associated with Psychiatric Illness (TiC-P)	✓	–	✓	✓
Training and acceptability	Client Satisfaction Questionnaire (CSQ-8)	–	✓	–	–

*T1, baseline; T2, post-intervention; T3, 6-month follow-up; T4, 12-month follow-up*.

#### Response

To determine the numbers of participants achieving a reliable positive outcome, we will code participants as responders or non-responders according to the widely used reliable change index (RCI) (73) after participation in the intervention. Participants will be considered responders when they display an RCI score of above 1.96.

### Statistical Methods

Data will be analyzed on an intention-to-treat basis including all participants who will be randomly assigned to conditions. Additionally, study completer analyses including only participants who filled out the questionnaires and intervention completer analyses including only participants who have completed at least four out of six sessions will be conducted. Missing data will be handled using multiple imputations (MIs) calculated by a Markov Chain Monte Carlo multivariate imputation algorithm of 100 estimations per missing value. MI is especially robust with respect to missing data. We will conduct an ANCOVA to examine differences in the primary outcome. To detect differences between the two study groups, we will conduct univariate analysis of covariance to compare secondary outcomes at post-treatment and 6- and 12-month follow-up adjusting for baseline scores. Predictors and mediators of changes of the primary outcome will be analyzed on exploratory basis using linear regression. For all analyses on continuous measures, Cohen's d (74) will be calculated by standardizing the differences between baseline and follow-up scores by the pooled standard deviation of the baselines scores.

The response rates will be compared across conditions with the help of contingency tables and Chi-Squared tests. For primary analysis, significance levels will be set at 0.05, one-sided. For the explorative analysis of the data, the significance levels will be set to 5%. All analyses will be performed with IBM SPSS v. 24.

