#### Assessment of Eligibility and Randomization

After registering with a self-chosen email address, applicants will receive an email with detailed information about the study procedure. They will be further informed that it is possible to withdraw from the intervention and/or study at any time without any negative consequences. Applicants are asked to complete an online screening questionnaire and to sign the informed consent form and return it by post or email. As soon as participants have completed the baseline assessment and meet the inclusion criteria, they will enter the study and will be randomized to one of the two study conditions. Participants are randomized to either the guided intervention group or a WCG in a 1:1 ratio. Randomization is performed by a research assistant not otherwise involved in the study using block randomization with varying block sizes. Once randomization has been completed, participants in the intervention group receive immediate access while participants in the control group receive access 12 months later.

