### Assessment and Data Management

Self-reports will take place at screening (T0), baseline (T1) prior to randomization, post-intervention (T2) 7 weeks after randomization, at 6- (T3) and 12-month follow-ups (T4; see Figure 1 for a detailed overview). Self-reported data will be collected using a secure online-based assessment system (AES, 256-bit encrypted).

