### Sample Size Calculation

To answer the research question described above, we aim to include 130 participants. That is to statistically detect a medium effect of (Cohen's d) *d* = 0.60, with a power (1–β) of 80% and an α of 0.05 (two-tailed test) for an intention-to-treat analysis using G^*^Power (75). The estimated effect of (Cohen's d) *d* = 0.60 is based on recent meta-analyses on the effects of treatments on internet addiction which shows rather high effect sizes for CBT (16) as well as several other psychological treatments (76).

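### The supplementary intervention-completer analysis has no usable control group as stated; comparing intervention completers with all controls is not a randomized comparison and is likely, though not certain, to favour the intervention

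*Protocol article*

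**What the plan says.** Under Statistical Methods, the main analysis is by intention to treat: "Data will be analyzed on an intention-to-treat basis including all participants who will be randomly assigned to conditions". Two supplementary analyses follow. One is defined by questionnaire response: "Additionally, study completer analyses including only participants who filled out the questionnaires". The other is defined by use of the intervention: "intervention completer analyses including only participants who have completed at least four out of six sessions will be conducted". The second rule names no arm, does not say which controls enter, and sets no date by which the four sessions must be done.

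Under Assessment of Eligibility and Randomization, "Participants are randomized to either the guided intervention group or a WCG in a 1:1 ratio", and "participants in the intervention group receive immediate access while participants in the control group receive access 12 months later". Under Assessment and Data Management, the outcome assessments are "post-intervention (T2) 7 weeks after randomization, at 6- (T3) and 12-month follow-ups". Under Sample Size Calculation, "we aim to include 130 participants", which is 65 per arm.

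The Discussion says that treatment motivation is typically low in this population and that guided interventions of this kind demand considerable self-regulation. The article gives no expected completion rate and no figure linking completion to outcome.

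**The concern.** The rule can be taken in two ways, and neither gives a sound between-group comparison.

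Applied to everyone, it removes the control arm, because controls have nothing to complete before the last assessment. Applied to the intervention arm only, it compares people who stayed for at least four sessions with every control, including those who would have dropped out had they been offered the programme. Randomization balances the two arms as wholes. It does not balance a self-selected part of one arm against the whole of the other.

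In this trial the selecting trait is close to the outcome. The article defines the disorder as an inability to control internet use, the Internet Addiction Test (IAT) covers loss of control, and completing the programme takes self-regulation. People able to finish may therefore do better on the IAT anyway, and adjusting for baseline IAT need not remove that.

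What is at stake is one supplementary result. Printed beside the intention-to-treat estimate, it could be read as the effect in those who took the treatment, and Statistical Methods carries no caution against that reading.

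**Working it through.** The article states no figure for the completer analysis, so there is none to reproduce.

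**Step 1. Who can meet the rule.** Controls receive access at 12 months; assessments fall at 7 weeks (T2), 6 months (T3) and 12 months (T4).

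| Assessment | Controls able to have completed four sessions |
|---|---|
| T2 | 0 of 65 |
| T3 | 0 of 65 |
| T4 | in practice 0 of 65, since access opens only then |

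**Step 2. Bias of completers versus all controls when the treatment does nothing.**

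Inputs:
- From the article: 65 per arm, ANCOVA adjusting for baseline, and a one-sided 5% level. The article sets that level for the primary analysis. For exploratory analyses it says 5% without stating sidedness.
- Assumed: completion share p = 0.5–0.7; correlation of completion with an unmeasured motivation trait 0.7; correlation r of that trait with lower T2 IAT 0.2–0.4; correlation of baseline with T2 IAT 0.5.

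If completers are those whose latent propensity exceeds c = z(1 − p), their mean propensity is φ(c)/p, so

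bias (in SD) = 0.7 × r × φ(c)/p.

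The residual SD after baseline adjustment is √(1 − 0.5²) = 0.866, so

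SE ≈ 0.866 × √(1/(65p) + 1/65).

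The one-sided 5% rejection rate is approximately Φ(bias/SE − 1.645).

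| p | φ(c)/p | SE | Bias, r = 0.2 | Rejection | Bias, r = 0.4 | Rejection |
|---|---|---|---|---|---|---|
| 0.5 | 0.798 | 0.186 | 0.11 | 15% | 0.22 | 33% |
| 0.6 | 0.644 | 0.175 | 0.09 | 13% | 0.18 | 27% |
| 0.7 | 0.497 | 0.167 | 0.07 | 11% | 0.14 | 21% |

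Simulation under the same assumptions agrees: a spurious benefit of d = 0.07–0.22 and rejection in about 11–32% of trials. In the same simulated data, intention to treat rejects in about 4–6%, and the intention-to-treat difference divided by the completion share averages within about 0.02 of zero.

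**Step 3. Sensitivity of the direction.** A second calculation correlates completion propensity directly with outcome (ρ) and uses no baseline covariate, so bias = ρ × φ(c)/p. At p = 0.6:

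| ρ | Bias (SD) | One-sided 5% rejection |
|---|---|---|
| −0.2 | −0.13 | about 1% |
| 0 | 0 | about 5% |
| 0.1 | 0.06 | about 9% |
| 0.2 | 0.13 | about 15% |
| 0.3 | 0.19 | about 24% |

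Over p = 0.5–0.9 and ρ = 0.1–0.4 the bias runs from 0.02 to 0.32 SD. A negative ρ would arise if people who improve early stop before session four.

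**Step 4. What the alternative costs.**

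*Precision.* Under the Step 2 assumptions the intention-to-treat SE is 0.866 × √(2/65) = 0.152. The complier-average SE is roughly 0.152/p: 0.30, 0.25 and 0.22 at p = 0.5, 0.6 and 0.7, against 0.19, 0.18 and 0.17 for the completer contrast.

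*Partial completion.* Suppose 60% complete and gain 0.60, and everyone else gains 0.30 (all assumed). Intention to treat gives 0.6 × 0.60 + 0.4 × 0.30 = 0.48. The complier-average estimate is 0.48/0.60 = 0.80, above the true 0.60. The completer contrast at r = 0.3 gives 0.60 + 0.7 × 0.3 × 0.644 = 0.735, or about 0.74. In this case both overstate the effect, and the complier-average estimate does so by more.

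**The case against.** **The empty control arm is a wording gap.** The label itself presupposes exposure to the intervention, and the evident intent is intervention-arm completers against all controls. Which controls enter could sit in an analysis plan that is not shown. A reader might infer that the sponsor means to run an analysis without controls; the article does not support that. What remains is that the article fixes the threshold and commits to the analysis, the rule does not work as stated, and its natural repair is not a randomized comparison.

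**The analysis is supplementary.** Intention to treat comes first and the trial is sized for it. No hypothesis or stated conclusion depends on completers. This stands in full. A reader might infer that the trial's main conclusion is compromised, and it is not.

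**The direction is assumed.** A reader might infer a certain bias toward benefit. The Discussion's remark on motivation and self-regulation makes that plausible, but the article gives no completion rate or correlation, and Step 3 shows zero or reversed bias under other inputs. This also stands. The loss of comparability does not depend on the direction.

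**The replacement has its own assumption.** Calling the complier-average estimate unbiased is justified only when the treatment has no effect, because then partial use cannot matter. Sessions 1 to 3 cover goal setting, impulse control and problem solving, and the behaviour-change plan begins in session 2, so one to three sessions may well help. Step 4 shows the resulting overstatement. The objection stands as a limit on the fix. It does not make the completer contrast a randomized one.

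**Conclusion.** The concern holds in a limited form. Controls cannot meet the four-session rule, and the workable reading is a non-randomized contrast that is likely, but not certain, to favour the intervention. The timetable alone shows the first part, and the one-arm selection shows the loss of randomization. The size depends on assumed inputs: about d = 0.07–0.22 of spurious benefit and about 11–32% false positives at a one-sided 5% level, for 50–70% completing and a motivation–outcome correlation of 0.2–0.4. The bias is zero if completion is unrelated to prognosis. The harm is confined to over-reading a supplementary result.

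**What to change.** Estimate the effect of completion as a complier-average causal effect by two-stage least squares:
- instrument: randomized arm;
- exposure: at least four of the six core sessions completed by T2, a cut-off that also supplies the missing date;
- covariate: baseline IAT;
- population: all randomized participants, in the same imputed data sets as the intention-to-treat analysis.

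State with the result that it assumes fewer than four sessions have no effect. Check this by repeating the model with any session started, or the number of sessions completed, as the exposure.

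If completers versus all controls is kept, say which controls enter and report it only as a non-randomized, exploratory description.

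Cost: one additional model plus its sensitivity versions, using session data that the Guidance section says are already monitored. The confidence interval is wider than for the completer contrast (SE ratio about 0.30/0.19 = 1.6 at 50% completion and 0.22/0.17 = 1.3 at 70%, under the assumptions above). The estimate is biased upward if partial completion helps.

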Treating IUD via the internet may appear contradictive at first. However, there are many arguments supporting this approach: (1) Reaching the target group through their common online setting could be effective as the internet is easily accessible and attractive. (2) Since the target group usually shows low levels of treatment motivation (19), an easily accessible and attractive treatment option is crucial; thus, a low-threshold intervention with interactive audio-visual content may facilitate access and reduce burdens of help-seeking. (3) Due to the individually tailored and adaptable content, a variety of symptoms associated with IUD such as procrastination, bad sleep patterns or alcohol consumption can be addressed. Based on these comorbid symptoms, secondary outcome measures were chosen to assess a reduction in symptoms associated with IUD that were targeted in the intervention. (4) Internet- and mobile-based interventions might be a feasible means to provide evidence-based treatment on a large-scale basis, since they have been shown to be effective in the treatment of numerous mental health disorders (20–23). Therefore, internet- and mobile-based interventions could be a way to reach individuals with IUD better than traditional approach. To the best of our knowledge, this is the first trial evaluating a guided internet- and mobile based intervention for IUD in an RCT design.

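### The primary test is set at 0.05 one-sided but the trial was sized at 0.05 two-tailed, so the error rate towards benefit is 5% rather than the 2.5% the sizing implies

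*Protocol article*

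**What the plan says.** The primary outcome is IAT symptom severity at 7 weeks, compared between arms by ANCOVA (Abstract; Statistical Methods). The decision level is given in Statistical Methods: "For primary analysis, significance levels will be set at 0.05, one-sided".

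The Sample Size Calculation section states "we aim to include 130 participants", to detect a "medium effect of (Cohen's d) *d* = 0.60" with 80% power and "an α of 0.05 (two-tailed test) for an intention-to-treat analysis". Allocation is equal (Assessment of Eligibility and Randomization: "Participants are randomized to either the guided intervention group or a WCG in a 1:1 ratio"), which gives 65 per arm.

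The hypothesis is directional: Aims of the Study and the Discussion both expect symptoms to fall. The article gives no reason for choosing a one-sided test, or for setting it at 0.05 rather than 0.025, and does not comment on the difference between the two sections.

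**The concern.** The two sections describe the same comparison at different levels of evidence. A two-tailed 0.05 test spends 0.025 on false claims of benefit; a one-sided 0.05 test spends 0.05. The trial was therefore sized to one standard and will be judged by a laxer one.

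The difference matters for results favouring the intervention with a one-sided p-value between 0.025 and 0.05, that is, a two-sided p-value between 0.05 and 0.10. In that range the headline conclusion depends on which level applies. The planned ANCOVA adds some ambiguity, because its F-test for group is non-directional. A one-sided rule needs that p-value halved when the effect is in the right direction, or an explicit directional contrast, and the article mentions neither.

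**Working it through.** **Inputs.** d = 0.60, power 80%, α = 0.05 two-tailed, N = 130 (Sample Size Calculation); 1:1 allocation, so 65 per arm (Assessment of Eligibility and Randomization); α = 0.05 one-sided (Statistical Methods). The article gives neither the correlation between baseline and 7-week IAT nor a dropout rate. The figures below therefore treat the comparison as an unadjusted two-sample t-test with complete data.

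**1. The plan's own figure.** Normal approximation, per arm: n = 2(z_α + z_β)²/d².

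- Two-sided 0.05: 2(1.960 + 0.842)²/0.36 = 43.6, so 44 per arm and 88 in total. The exact noncentral t calculation gives 45 per arm, 90 in total (power 80.4%).
- One-sided 0.05: 2(1.645 + 0.842)²/0.36 = 34.4, so 35 per arm and 70 in total. The exact calculation gives 36 per arm, 72 in total.

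Neither level reproduces 130. That total would fit a loss of about 31% applied to 90 (1 − 90/130 = 0.31), or d of about 0.50 two-sided (exact total 128), but the article states neither. This gap is a separate matter. What counts here is that 130 exceeds the requirement under both levels.

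**2. Error rate towards benefit.** Two-sided 0.05: 0.05/2 = 0.025. One-sided 0.05: 0.05. The ratio is exactly 2 and does not depend on sample size or model.

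**3. Smallest significant observed difference, 65 per arm.** Critical d = t × √(2/65), with 128 degrees of freedom and √(2/65) = 0.1754.

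- One-sided 0.05: 1.657 × 0.1754 = 0.291 SD.
- Two-sided 0.05: 1.979 × 0.1754 = 0.347 SD.

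**4. Power, 65 per arm.** At d = 0.60 the noncentrality is 0.60 × √(65/2) = 3.42. The normal approximation gives Φ(3.42 − 1.645) = 96.2% one-sided and Φ(3.42 − 1.960) = 92.8% two-sided. Exact t values:

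| True d | One-sided 0.05 | Two-sided 0.05 |
|---|---|---|
| 0.60 | 96.1% | 92.4% |
| 0.50 | 88.3% | 80.8% |

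A one-sided 0.025 test also gives 92.4% at d = 0.60.

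**5. Allowance for missing data.** If 31% of the 130 were lost and imputation recovered none of their information, about 90 would remain (45 per arm). Two-sided power at d = 0.60 would then be 80.4%, still at the stated target.

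**The case against.** The strongest defence is that only Statistical Methods states a decision rule. The sample-size section records a planning assumption, and sizing at a stricter level than the one tested is conservative for power. This stands in part. A reader might infer that the article contains two competing success criteria, so that a result passes in one section and fails in the other, or that the investigators could choose between them after seeing the data. The text does not support that: it designates one level for the primary analysis, the one-sided 0.05. What remains is that this level is laxer than the one used for sizing, and no reason is given.

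A second defence is the directional hypothesis. It is stated and gives a one-sided test some basis. It does not settle how much error belongs in that tail, and a one-sided test at 0.025 would serve the same hypothesis. It is also fair to say that the nominal type I error is 5% under both rules; the doubling applies only to the benefit direction.

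A third point concerns harm. A one-sided test cannot formally declare worsening, and a reader might take the Introduction's remark "Treating IUD via the internet may appear contradictive at first" as an admission that worsening is plausible. It is not one. The remark introduces four arguments in favour of internet delivery, and no section says that symptoms might worsen. The point does not rest on it.

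Finally, the thresholds and power figures ignore baseline adjustment and missing data. Adjustment would lower the thresholds and missing data would raise them, so they are approximations. The doubling of the benefit-tail error is not affected.

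**Conclusion.** The point holds. The primary analysis is to be tested at a level that allows a 5% chance of a false claim of benefit, while the trial was sized on 2.5%, and the article neither explains nor reconciles this. The practical reach is results with a one-sided p-value between 0.025 and 0.05: observed differences between roughly 0.29 and 0.35 SD, assuming an unadjusted t-test with 65 per arm and complete data.

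A reader might also infer that the mismatch leaves the trial underpowered. It does not: on that approximation, power at d = 0.60 exceeds 92% under either level. The fault is a looser standard of evidence for the primary claim, not a shortage of participants.

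**What to change.** In Statistical Methods, replace the one-sided 0.05 level with a two-sided 0.05 level for the primary analysis, matching the Sample Size Calculation section. A one-sided 0.025 level would be equivalent in the benefit direction; if it is preferred, both sections should state it. Enrolment began in September 2018, so the change should be made by a dated, documented amendment before the primary analysis.

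The cost is one sentence plus the amendment. N = 130 need not change. The power stated in the article is already for a two-tailed test, so that statement is unaffected. Relative to the one-sided rule, power at d = 0.60 falls from 96.1% to 92.4% on the complete-data approximation, and about 90 participants with complete data already give the stated 80%.
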